### Sample size

Resources allow us to recruit 36 participants to our study. Although this number is relatively small it will allow us to gain measures of trial feasibility (such as recruitment rates) and an estimation of the variance following dropout. Sample size estimates for effect size (ES) calculation may start from a total *N* of 24 [17]. However, ES calculated from small samples are sensitive to inflation [18] and we will take this inflation factor into account when conducting a power analysis for a larger trial.

### Randomisation

Randomisation will be carried out after consent to participate in the trial has been given and the baseline assessment has been carried out. Participants will be randomised through an independent web-based service provided by UKCRG registered King’s Clinical Trials Unit (Reg. No. 053). The randomisation procedure will employ methods to maintain pre-randomisation allocation concealment. We will stratify by site for logistical reasons, so that treatment cases are equitably allocated across sites.

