## Methods

### Participants and setting

We aim to recruit 36 adults aged 18 years or over, presenting to the Promoting Recovery Service Community Mental Health Teams of the Psychosis Clinical Academic Group of the South London and Maudsley NHS Foundation Trust (SLaM) within King’s Health Partners. Ten teams, from the inner-London boroughs of Lambeth and Southwark are participating. The sample will include service users with diagnoses of bipolar affective disorder and schizoaffective disorder. A recent local audit showed that of 1344 adults currently treated in SLaM with a diagnosis of bipolar disorder, more than half (*N* = 823) are being treated within psychosis services, with around 200 in each borough (13–20% of the caseload). As such, we expect recruitment to be reasonably straightforward.

The proposed sample size, while representing only a small proportion of the caseload, is in line with recommendations for the number of participants required to estimate variance in outcomes and is, therefore, appropriate for an early stage feasibility study. (24 to 50 participants [17, 18]). The feasibility study is designed to feed into a second larger pilot study, which will benefit from feedback received in the current study, and allow consideration of the representativeness of the study sample.

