### Statistical analysis

In accordance with the Consolidated Standards of Reporting Trials (CONSORT) principles, we will report all participant flow in the study. The aim of the analysis will be to describe the feasibility and acceptability of the trial ACT/PE intervention and estimate effect sizes for group differences in attitude, adherence, clinical and quality of life outcomes. Binary outcomes will be analysed using logistic regression, chi-square or Fisher’s exact test if expected values were small. Continuous outcome scores will be analysed using analysis of covariance (ANCOVA) models in which the mean group difference will be adjusted for baseline outcome scores. Clustering for patients within therapy groups will be accounted a random effect for cluster in the ANCOVA models. Effect sizes will be derived from standardised regression coefficients in which treatment group differences, adjusted for outcomes scores at baseline, will be divided by the standard deviation of the outcomes. Following Cohen’s guidelines, effect sizes will be treated as small (ES = 0.2), moderate (ES = 0.5) or large (ES = 0.8).

As a pilot study, the sample size may not give sufficient power to reject null hypotheses; however, we will derive inferential statistics on the intention-to-treat principle. As the sample size is small and regression assumptions may not be met and we will use robust methods, such as bootstrap resampling, to derive standard errors and bias-corrected accelerated confidence intervals. Missing data will be described per outcome and if possible mechanisms driving missingness accounted for in the statistical model under the assumption that data is missing at random and with sensitivity analyses. All statistical tests will be two-sided and confidence interval level set at 95%. STATA 14.1 (StataCorp, College Station, TX, USA) will be used to analyse the data.

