## Discussion

We have adhered to Standard Protocol Items: Recommendations for Interventional Trials (SPIRIT) [31, 32] guidance in devising and reporting our protocol (Fig. 2; SPIRIT Checklist with information sheets and consent forms for participants are included as an Additional file 1). The trial is funded until the end of July 2018. The study will be the first study of its kind examining ACT and psychoeducation groups for people with bipolar disorder and/or symptoms. Should the intervention prove feasible, acceptable and potentially helpful cost-effective addition to routine care, we will apply for funding for a larger-scale evaluation. If outcomes suggest that the intervention does not show promise in terms of potential clinical improvement, we will continue to refine the intervention, based on participant feedback, further consultation, and our process measures, before attempting a further pilot. Findings will be limited by the pilot nature of the study, including the small sample size, location in a single service and opportunistic recruitment strategy. The therapy will be compared to treatment as usual and not to an alternative psychological intervention, so any effects found may be non-specific. We are not assessing longevity of effects in this study: further research will be required to ascertain longer-term outcomes.

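### Randomisation is stratified by site, but site is in neither the stated ANCOVA nor the bootstrap, so reported intervals are somewhat too wide if site is prognostic

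*Protocol article*

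**What the plan says.** Under Randomisation, the protocol article states: "We will stratify by site for logistical reasons, so that treatment cases are equitably allocated across sites". Allocation is 1:1 (Abstract, Methods). The Sample size section says "Resources allow us to recruit 36 participants to our study".

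Under Statistical analysis, continuous outcomes are to be analysed by "analysis of covariance (ANCOVA) models in which the mean group difference will be adjusted for baseline outcome scores". The next sentence adds a second term: "Clustering for patients within therapy groups will be accounted a random effect for cluster in the ANCOVA models". Because the sample is small, "we will use robust methods, such as bootstrap resampling, to derive standard errors and bias-corrected accelerated confidence intervals". Site appears in none of these three statements.

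The article does not say what a site is. Participants and setting reports: "Ten teams, from the inner-London boroughs of Lambeth and Southwark are participating". The Discussion lists "location in a single service" among the study's limitations. No statistical analysis plan is at hand.

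**The concern.** When treatment is balanced within sites, differences between sites cancel out of the treatment comparison. A model without site does not know this. It leaves the between-site variation in the residual and reports a standard error larger than the one the design delivers.

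The interval is one of this pilot's main products. Study aims asks how large any effect is and how variable it is likely to be, and Sample size says the effect sizes will feed a power analysis for a larger trial.

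The therapy-group random effect does not stand in for site. Participants in routine care have no therapy group until after the 14-week assessment (Study design; Intervention). If groups happen to run by site, which the article does not say, that term may absorb some site variation, but only in the active arm.

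The bootstrap does not settle it either. Ordinary resampling lets the numbers per arm within site vary from one resample to the next, so with site absent from the model it brings the between-site variation back in.

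**Working it through.** **The plan's own figure.** N = 36 is set by resources and lies inside the cited 24 to 50 range. It has no effect size, standard deviation or power behind it, so there is nothing to reproduce.

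**Inputs from the article.** N = 36, 1:1 allocation, stratification by site, ANCOVA on the baseline score, two-sided 95% intervals, and ten teams in two boroughs.

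**Assumed inputs.** ρ, the share of baseline-adjusted outcome variance lying between sites, from 0 to 0.30; and a baseline–outcome correlation of 0.5.

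**Step 1: approximation.** With balance within site, the true variance of the treatment difference is proportional to 1 − ρ, while the model without site reports a variance proportional to 1. So

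reported SE / true SE ≈ 1/√(1 − ρ).

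At ρ = 0.05 this is 1/√0.95 = 1.026; at ρ = 0.10 it is 1/√0.90 = 1.054.

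**Step 2: simulation.** There were 8,000 runs per setting with N = 36, equal allocation within site and complete data, fitting ANCOVA with and without site as a fixed effect. The CI ratio is the 95% interval width without site divided by the width with site.

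| ρ (assumed) | 1/√(1 − ρ) | CI ratio, two sites | CI ratio, ten sites | Type I error without site, two sites | Type I error with site, two sites |
|---|---|---|---|---|---|
| 0 | 1.000 | 0.998 | 0.983 | 0.050 | 0.052 |
| 0.02 | 1.010 | 1.009 | 0.993 | 0.044 | 0.047 |
| 0.05 | 1.026 | 1.026 | 1.008 | 0.044 | 0.049 |
| 0.10 | 1.054 | 1.056 | 1.032 | 0.040 | 0.051 |
| 0.20 | 1.118 | 1.123 | 1.092 | 0.026 | 0.047 |
| 0.30 | 1.195 | 1.203 | 1.162 | 0.020 | 0.049 |

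Monte Carlo error on a type I rate near 0.05 is √(0.05 × 0.95/8000) = 0.002.

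**Step 3: estimator or reported error?** With two sites, the empirical SE of the treatment estimate is the same with and without site: 0.333 in both at ρ = 0.05, and 0.299 in both at ρ = 0.20. What differs is the SE the model reports. At ρ = 0.20 it is 0.339 without site and 0.301 with site. At ρ = 0.05 it is 0.336 and 0.327; the empirical 0.333 carries simulation error of about 0.333/√(2 × 8000) = 0.003, so the interval ratio is the better guide there.

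**Step 4: what site means.** Two boroughs give 36/2 = 18 participants per stratum, and residual degrees of freedom fall from 36 − 3 = 33 to 32. Ten teams give 36/10 = 3.6 per stratum, and fixed effects cost 9 df (33 to 24). In the ten-site column, fixed-effect adjustment makes intervals slightly wider at ρ of 0.02 or less.

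**Step 5: dropout.** With 20% of outcomes missing at random (assumed) and two sites, the CI ratio is 1.021 at ρ = 0.05 and 1.117 at ρ = 0.20, much as before.

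The therapy-group random effect and the bootstrap were not simulated.

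**The case against.** The strongest reply is that this is a condensed article. A full covariate list and the definition of strata are commonly left to a statistical analysis plan, and nothing in the article would conflict with adding site there. That limits the point but does not remove it. The article does state a model, with its covariate, its random effect and its method for standard errors, and the stratification factor is not in it.

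The size can also be challenged, fairly. The article gives no between-site variance, and its reason for stratifying is logistical, not prognostic. A 3% wider interval would not change any conclusion from a 36-person pilot that already concedes limited power. By a simple two-sample calculation, 18 per arm gives 80% power only for a standardised difference of about 0.93, so N is the main constraint.

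Four stronger readings are tempting, and the document does not support them:

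- *That the model adjusts for the baseline score alone.* It also has the therapy-group random effect.
- *That information is lost, as if some of the 36 participants were thrown away.* With balanced, complete data the estimate is as precise either way; only the reported interval is too wide. There is no added false-positive risk.
- *That the article contradicts itself on site.* Site as a stratifier appears only under Randomisation. The teams and boroughs describe the setting, and the single service is a limitation on generalisability. The term is undefined, not inconsistent.
- *That small strata would leave most blocks incomplete.* No blocking scheme or block size is stated.

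**Conclusion.** The point holds as a minor mismatch between design and analysis. Following the article as written, intervals for continuous outcomes are too wide whenever site is prognostic. With two sites the excess is about 1% to 3% if site carries 2% to 5% of the baseline-adjusted variance, about 6% at 10%, and 12% to 20% only at 20% to 30%. If site is not prognostic, nothing of consequence changes.

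The direction follows from the design. The size rests on assumed between-site shares, on balanced allocation within site, and on a model without the therapy-group random effect or the bootstrap. The form of the correction cannot be fixed until the site levels are stated.

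**What to change.** - **State the site levels actually used in the randomisation system.** The factor should be reported, not redefined: the Status section dates the first randomisation to 10 May 2017.
- **Include that factor in the ANCOVA models for continuous outcomes**, alongside the baseline score and the therapy-group term: as a fixed effect if it is the two boroughs, or as a random effect if it is the ten teams, which avoids spending 9 df.
- **Resample within site in the bootstrap.**
- **For binary outcomes, add site only where event counts allow a logistic model.** Fisher's exact test, which the article keeps for small expected values, takes no covariates, and extra logistic terms with 36 participants risk separation.

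The cost is a few sentences in the analysis section and, for two boroughs, one degree of freedom. No change to recruitment, allocation or data collection is needed.

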### Blinding procedure

We will not be able to blind participants to treatment group. Similarly, the therapists cannot be blind to allocation as they will deliver the intervention. However, the research workers completing the outcome measurements will be blinded to treatment allocation. Should they be accidentally unblinded during the assessment, we will record which outcomes were completed blind and allocate a new assessor for any subsequent assessments. Post-randomisation assessors will work separately from the research and clinical teams to minimise the likelihood of unblinding. We will report any instances of unblinding in subsequent publications. The end of the trial will be defined as the last follow-up at 14 weeks. The trial statistician will also be blinded to treatment group for the analysis of clinical and functional outcomes.

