#### Intervention

The ACT/PE intervention will consist of ten groups, each running over ten consecutive weeks, followed by a booster session, 4 weeks later. Each group session will last for 2 h. The intervention will be delivered in addition to routine care (specialist care coordination, medication, practical and emotional support), and will be compared to routine care alone (TAU). After the 14-week assessment, individuals in the routine care condition will be offered the intervention.

The ACT/PE intervention will focus on psychoeducation approaches to understanding bipolar and mood disorders. Each session will focus on a different issue pertinent to bipolar disorder; including, mania, stress, sleep, depression, medication, communicating with friends and family, and relapse prevention. Each session will introduce ACT skills as a different way of responding to symptoms of bipolar disorder. The Balancing ACT groups are designed to be interactive with experiential exercises throughout and a commitment to work towards a valued goal, and the practice mindfulness exercises in between sessions.

We acknowledge that 14 weeks is a relatively short timeframe to assess change. For the pragmatic purposes of this study, because we are interested in the potential helpfulness of the intervention, rather than the longevity of the effects, we consider this time period appropriate. ACT has been shown to achieve change in brief interventions: previous studies from our research group [20] have shown significant change in 12 weeks during ACT interventions with clients with psychosis. This is longer than ACT interventions would normally be, but consistent with psychoeducation groups for people with bipolar disorder [6–8]. A future study can address maintenance of effects over time.

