### Data management

We will use paper assessment packs and enter data into electronic databases which include: (1) baseline demographics, (2) repeated clinical measures, (3) sessional therapy measures and (4) therapy delivery and adherence. Outcome assessments will be carried out by researchers who do not have access to therapy or feedback data. Data will be checked and cleaned against original paper copies and a final database returned to the statistician, who will combine with allocation data for analysis.

Patient data will be pseudonymised for the duration of the study and fully anonymised thereafter. Fully identifiable personal details will be kept on paper in a locked filing cabinet in a locked or occupied office; on secure NHS computers; and encrypted on password-protected computers. All trial data will be stored in line with the Data Protection Act [30].

The allocation database will be accessible only to the study randomiser (who will not conduct post-baseline assessments) and the trial statistician until the study is completed.

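### The trial statistician is declared blinded for the analysis, but the data-management plan gives that role the allocation database and the merge, so the claim cannot hold as written

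*Protocol article*

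**What the plan says.** Four sections of the protocol article bear on this.

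- **Blinding procedure** closes with the claim: "The trial statistician will also be blinded to treatment group for the analysis of clinical and functional outcomes".
- **Data management** describes the data flow. After checking and cleaning there is "a final database returned to the statistician, who will combine with allocation data for analysis". The allocation database is "accessible only to the study randomiser (who will not conduct post-baseline assessments) and the trial statistician until the study is completed". The same section lists four electronic databases, two of which hold sessional therapy measures and records of therapy delivery and adherence.
- **Statistical analysis** specifies ANCOVA adjusted for the baseline score for continuous outcomes, and adds: "Clustering for patients within therapy groups will be accounted a random effect for cluster in the ANCOVA models".
- **Intervention** fixes when controls can join a therapy group: "After the 14-week assessment, individuals in the routine care condition will be offered the intervention".

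The article does not mention coded arm labels, a second statistician or data manager who holds the allocations, or a point at which the statistician's blind is broken.

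**The concern.** The role declared blind for the analysis also has access to the allocations during the study and attaches them to the outcomes for that same analysis. The two sections cannot both describe what will happen.

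Blinding an analyst is meant to ensure that modelling and missing-data decisions are made without knowing which way they move the treatment effect. Some of that discretion is visible in the article. Missingness mechanisms are to be modelled where feasible, robust methods are given by example, and sensitivity analyses are announced without being specified. The article also says that the effect sizes will inform the power analysis for a larger trial, and that a funding application depends on whether the intervention looks promising. If those decisions are taken with allocation in view, a report that repeats the blinding sentence would describe a safeguard that was not in place.

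**Working it through.** No arithmetic bears on the contradiction, so the check sets the statements side by side.

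**1. Access during the study.** Data management names two roles with access to the allocation database before completion: the study randomiser and the trial statistician. Blinding procedure defines the end of the trial as the last 14-week follow-up. The statistician is therefore allowed to see allocations while outcomes are still being collected. The sentence permits access and does not say that the statistician will use it, so on its own it weakens the blinding claim without refuting it.

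**2. The merge.** The statistician receives the final database and joins it to the allocation data for analysis. This goes beyond permission: the person who does the join has the treatment variable in hand when the analysis starts, which is the moment for which Blinding procedure claims blindness.

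**3. Could the allocation data be masked codes?** This is the only reading that would reconcile the sections. The article does not state it. Access is limited to two roles, and the randomiser is kept away from post-baseline assessments. Those precautions make most sense if the database shows real allocations.

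**4. Would masked codes be enough?** Not with the stated model.
- The last outcome assessment is at 14 weeks, and controls are offered the groups only after it. For every outcome in the analysis, therapy-group membership therefore exists in one arm only.
- With 36 participants randomised 1:1, about 36 / 2 = 18 people would share therapy-group codes and about 18 would have none.
- In the usual codings, controls have a missing code, form single-person clusters or share one common cluster. Each pattern identifies the arm that received therapy.
- Hiding this would take an extra step, such as artificial group codes for controls supplied by someone else. The article describes no such step.
- The sessional and adherence databases would identify the arm in the same way if they go to the statistician. The article does not say whether they do, so this is a secondary point.

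**5. Is early access needed?** Data monitoring states that there is no interim analysis and no separate Data Monitoring Committee. Nothing in the article requires the statistician to hold allocations before database lock.

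**6. What is unaffected?** Randomisation runs through an independent web-based service with concealment before allocation. Post-randomisation assessors are blinded, work separately from the research and clinical teams, and have no access to therapy data. None of this depends on the statistician's access.

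**The case against.** The best defence has four parts.

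**The text is about access, not the form of the data.** Data management does not say in what form the allocation is stored, and the merge follows checking and cleaning, so cleaning decisions are not shown to be unblinded. Both points are fair. They are why the conclusion is that the claim cannot hold as written, and not that allocations are known to have influenced anything.

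**Full analyst blinding is hard whenever only one arm is clustered.** This is true, and it is a reason to qualify or withdraw the sentence. It does not reconcile the sentence with the data flow.

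**This is a small pilot.** It describes feasibility and estimates effect sizes, the article concedes that power may be insufficient, and the more important protections stand. This limits the severity: the point should be fixed, but the trial does not hinge on it.

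**A statistical analysis plan may settle the details.** Missing-data and bootstrap details commonly belong there and are not faulted here. An unseen plan would not remove the conflict between two published statements.

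Two stronger readings are tempting and are not supported. A reader might infer that an unblinded statistician inflates the type I error by choosing between the 10- and 14-week results. That freedom comes from having two visits with no named primary one. With a two-sided test, an analyst who saw only coded arms could use it equally well, so it does not measure the effect of unblinding. A reader might also infer that the choice between logistic regression, chi-square and Fisher's exact test lets the analyst move the main result. That choice concerns binary outcomes only. The primary outcome, the Brief QoL.BD, is a continuous score for which baseline-adjusted ANCOVA is fixed.

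**Conclusion.** The concern holds as an internal inconsistency that should be fixed. The blinding claim conflicts with the statistician's access and with the merge, and the therapy-group term would reveal the active arm even under coded labels.

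No numerical size can be attached. The documents give no basis for estimating how far knowledge of allocation would shift the estimate, and they do not show that it would. The practical effect is moderate: a possible misstatement in the report, and some analyst discretion exercised with allocation in view.

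The conclusion rests on two assumptions: that the allocation database holds real allocations, since the article says nothing of codes, and that the therapy-group variable is coded in one of the usual ways. If the first assumption fails, step 4 of the check still stands. It would take both masked arm codes and disguised group codes to rescue the sentence, and the article describes neither.

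**What to change.** **Data management.** Remove the statistician's access to the allocation database until database lock. Leave it with the study randomiser, who already has access, or with the randomisation service. The statistician can still do the merge, but after lock.

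**Blinding procedure.** Replace the final sentence with wording such as: The statistician will finalise the model choices, missing-data choices and analysis code before allocation and therapy-group codes are released. Release follows database lock, and the final analysis run is not blinded.

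If the access change cannot be made, the minimum is to withdraw the claim of a blinded statistician, here and in the trial report.

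**Cost.** Two wording changes and one change of access rights, plus finishing the code before release. The article describes the Clinical Trials Unit only as providing randomisation, so its ability to hold and release codes would need confirming. Leaving them with the study randomiser avoids that question. Sample size, assessments and the planned model do not change.
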